## Abstract

**Background:**

*Pudilan Xiaoyan* oral liquid (PDL) is a proprietary Chinese medicine preparation widely used for upper respiratory tract infection, known for its significant therapeutic effects. However, the safety profiles reported in several observational studies vary, and these studies primarily focus on efficacy rather than specifically addressing safety concerns, thus representing inadequate safety monitoring.

**Objective:**

This study aimed to investigate the incidence of adverse drug reactions (ADRs) associated with PDL and explore the factors contributing to these reactions.

**Methods:**

The study is a prospective, observational, multicenter, hospital-based surveillance study. A total of 17 hospitals from China are involved. The study is expected to enroll a large sample of 10,000 patients aged between 18 and 80 years with upper respiratory tract infection who were prescribed PDL. The patients’ data, including demographics, medical history, diagnostic information, medication details, adverse events, and laboratory test results, will be monitored. The occurrence of ADRs will be recorded. The primary outcome is the incidence of ADR. Secondary outcomes are the ratio of patients whose body temperature return to the normal range (cases of body temperature normalization and the duration for achieving normal body temperature within a 3-day period will be documented) and changes in liver and kidney function (occurrence of drug-induced liver injury and acute kidney injury). Descriptive analyses will be performed for the primary and secondary outcomes. A cohort, nested, case-control study design will be used. If one patient has an ADR, then 4 patients without ADRs will be matched as the control group according to gender, age within 5 years, drug batch, and other factors, at a ratio of 1∶4 to compare the symptoms related to ADRs. The differences of ADR incidence among the possible influencing factors will be compared separately to find the factors with large differences. Then, synthetic minority oversampling technique and group least absolute shrinkage and selection operator methods will be used to identify factors influencing the occurrence of ADRs. Finally, propensity scoring methods will be used to control for confounding variables. The progress of each subcenter will be closely monitored, and the incidence of ADR will be systematically calculated. Furthermore, the characteristics and influencing factors of ADR will be analyzed, along with an investigation into its geographical distribution.

**Results:**

The study began on July 17, 2019. Due to the limited number of eligible patients, missed follow-ups, and the huge clinical burden caused by public health events in 2019, the final case will be enrolled on August 30, 2025.

**Conclusions:**

This study will obtain safety results of PDL in the real world and provide guidance on the clinical safety of traditional Chinese medicine formulations.

**Trial Registration:**

ClinicalTrials.gov NCT04031651; https://clinicaltrials.gov/study/NCT04031651

**International Registered Report Identifier (IRRID):**

DERR1-10.2196/65789

## Introduction

Upper respiratory tract infection (URTI) involves inflammation of the respiratory mucosa from the nose to the lower respiratory tract; it causes localized symptoms that constitute several overlapping syndromes: pharyngitis, common cold, sinusitis, and bronchitis [1]. Bacterial or viral infections may be the cause of URTI, but antibiotics are recommended only for the former [1]. It is a self-limiting viral infection [2]. Currently, considering the treatment of symptoms for URTI and anti-infective therapy [3], the efficacy remains unsatisfactory with notable adverse reactions [4]. *Pudilan Xiaoyan* oral liquid (PDL) is a Chinese patent medicine, collected in the *Chinese Pharmacopoeia*. It has been widely used for URTI and has obtained good curative effect [5,6]. It contains drugs such as *Scutellaria baicalensis*, *Corydalis bungeana*, *Taraxacum mongolicum*, and *Isatis indigotica* [7]. All four herbs have the traditional Chinese medicine effects of removing heat and toxic materials, cooling blood, and reducing swelling. Besides, they also have anti-inflammatory, analgesic, antibacterial, and other biological effects [8]. Despite the efficacy of PDL, it is also necessary to monitor its safety.

In terms of safety, among the biological mechanisms of PDL, *S baicalensis*, *C bungeana*, *T mongolicum*, and *I indigotica* have been identified as herbs with low toxicity. The aforementioned drugs, however effective, are associated with gastrointestinal adverse reactions due to their bitter cold properties. Additionally, *S baicalensis* exhibits limited embryotoxicity and hepatotoxicity and can induce allergic reactions leading to vesicular eruptions [9]. *T mongolicum* primarily contributes to reversible toxicity targeting red blood cells [10], while *I indigotica* possesses nephrotoxic properties and may impose a burden on the urinary system with prolonged use [11]. The formulation of *C bungeana* contains certain hepatotoxic effects [12]. Therefore, it is necessary to investigate the safety of PDL since it is composed of the aforementioned herbal groups.

Monitoring the unintended effects of a drug (pharmacovigilance or drug safety) is crucial due to limited knowledge of rare or late-stage side effects upon market release of new drugs [13,14]. In recent years, numerous related studies have reported the clinical efficacy of PDL; however, there were few independent safety studies on it, most of which were small scale and exhibited significant variations in reported safety outcomes across different studies [15-18], resulting in inadequate understanding of its safety monitoring. In summary, published safety data on adverse effects of PDL therapy were insufficient, thereby impeding the use of standardized recommendations that are necessary for ensuring drug safety.

Although Chinese patent medicine generally exhibits a low incidence of adverse reactions, the evidence pyramid classification derived from effectiveness evaluations primarily considers randomized controlled trials as high-level evidence. However, this classification standard may not fully meet the evidence requirements for postmarketing drug safety evaluation due to limitations such as short intervention courses or small sample sizes, often resulting in an inability to detect ADRs and differences between groups. For the above reasons, this study intends to adopt a large-scale, multicenter, long-term, noninterventional, observational study design to comprehensively analyze and report on the occurrence of adverse events (AEs) [19].

The mechanism of kidney metabolism and excretion of various drugs and toxins is an important cause of drug nephrotoxicity [20], while studies have shown that most of the AEs related to the urinary system were from treatment with PDL [21]. It can be seen that the kidney damage caused by PDL needs further investigation. As hepatic function plays an essential role in drug metabolism [22], clinical studies are necessary to determine the characteristics of PDL-related hepatotoxicity. Additionally, the influencing factors of other PDL-related adverse reactions are still unclear and may be related to the inherent characteristics of the drug itself, improper usage and dosage, improper combination, repeated administration, or use without indications, which need further investigation and study. Furthermore, a comprehensive study regarding the adverse effects associated with PDL use in patients is imperative to optimize the risk-benefit ratio and alleviate strain on limited health care resources.

## Methods

### Research Design

This is a prospective, observational, multicenter, hospital-intensive monitoring, and continuous registry study. We used the SPIRIT (Standard Protocol Items: Recommendations for Interventional Trials) checklist when writing our report [23]. The study flowchart is shown in Figure 1.

**Figure 1 figure1:**
[figure not shown]
Study flowchart. ADR: adverse drug reaction; CRF:case report form; PDL: Pudilan xiaoyan oral liquid.

**Figure 2 figure2:**
[figure not shown]
The geographical location of the 17 hospitals in China involved in this study.Light blue represents North China, light pink represents Central China and light green represents South China.

### Sample Size

In accordance with the requirements of the *Guide to Key Drug Monitoring for Manufacturing Enterprises* [24], and referring to the 2013 *Technical Specifications for Intensive Hospital Safety Monitoring of Post-Marketing Chinese Medicine* [25], the “rule of threes” was used for sample size calculation, which states that “if no specific event is observed in X existing cases, there is a 95% likelihood that the occurrence rate of such an event is ≤3/X.” Based on the detection rate of rare ADRs (1/10,000 to 1/1000), it is estimated that 3000 cases would need to be collected. However, due to the low probability of ADR occurrences investigated in this study, actual monitoring will be extended to 10,000 cases.

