### Outcome Measures

#### Primary Outcome Measure: Incidence of ADRs

The incidence of ADRs is the primary outcome measure, and we will identify factors that contributed to the occurrence of ADRs. The incidence of ADR will be primarily categorized in accordance with the criteria proposed by the Committee of International Organization of Medical Sciences: very common (≥10%), common (1%-10%, including 1%), occasional (0.1%-1%, including 0.1%), rare (0.01%-0.1%, including 0.01%), and very rare (<0.01%) [28], as well as according to the classification of ADR symptoms by the World Health Organization (WHO) [29]. The WHO classification of organs and systems involved in ADRs will also be referenced [30]. The incidence characteristics and regional distribution will be subsequently analyzed, while concurrently investigating the influencing factors (Table 2).

**Table 2 table2:** Centralized monitoring results of Pudilan Xiaoyan oral liquid in the registered hospitals.

Monitoring result	Description
Categorization	The ADR^a^ was categorized based on general, novel, and severe classifications The classification was based on the organs and systems affected by the ADR The symptoms of the ADR were classified
ADR incidence	The specific event features of each ADR included the incidence rates of various categories and whether they are infrequent or exceptionally rare
Pedogenic properties	Occurrence characteristics of ADRs specific to each category
Geographical distribution	The distribution of ADRs is primarily observed in North China, Central China, South China Each region exhibits distinct characteristics of ADRs
Influencing factors	Days of medication, age, drug combination, etc

^a^ADR: adverse drug reaction.

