##### Change in Liver Function

We will observe liver function in at least 3000 patients before and after medication. Liver function indexes will include alanine transaminase (ALT) and aspartate transaminase. To observe whether the above liver function indexes appear abnormal after medication, we will use the 2011 International Association for Severe Adverse Reactions–recommended biochemical diagnostic criteria for drug-induced liver injury [31]. Drug-induced liver injury is defined as meeting one of the following conditions:

ALT ≥5× upper limit of normal (ULN);Alkaline phosphatase ≥2×ULN, especially with 5’-nucleotidase or γ-glutamyl transpeptidase elevation, excluding alkaline phosphatase elevation caused by other diseases; orALT ≥3×ULN and total bilirubin ≥2×ULN.

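### The 3000 cases stated for rare ADRs of 1/10,000 to 1/1000 reach only 1/1000; the planned 10,000 reach 3/10,000, so the lower part of the rare class is not covered and very rare cannot be established

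*Protocol article*

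**What the plan says.** The Sample Size section of the protocol article quotes the rule of three in this form: "if no specific event is observed in X existing cases, there is a 95% likelihood that the occurrence rate of such an event is ≤3/X". It then gives the target and the result in one sentence: "Based on the detection rate of rare ADRs (1/10,000 to 1/1000), it is estimated that 3000 cases would need to be collected". The next sentence raises actual monitoring to 10,000 cases because the ADRs under study are improbable. It does not name the rate that 10,000 is meant to reach.

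The section on the primary outcome, incidence of ADRs, sorts incidence into five frequency classes. The two lowest are given as "rare (0.01%-0.1%, including 0.01%), and very rare (<0.01", the last figure being in per cent. Table 2 in that section says that the results for ADRs will include the "incidence rates of various categories and whether they are infrequent or exceptionally rare".

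**The concern.** The rare class runs over a factor of ten, from 1/10,000 to 1/1000, and the rule of three is inversely proportional to the rate. One sample size cannot satisfy the rule at both ends. The figure printed is the one for the more frequent end, yet the sentence attaches it to the whole range.

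Because the extension to 10,000 has no detection limit of its own, a reader may take 3000 as enough for the entire rare class and 10,000 as a margin beyond it. This study's main product is a frequency statement about ADRs. If its reach is overstated, the absence of a given ADR will be read as stronger evidence of safety than it is. The lowest class in the reporting scheme would also appear to be within reach when it is not.

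**Working it through.** **Inputs, all from the protocol article**
- Rule: zero events in X cases bound the rate at 3/X with 95% confidence (Sample Size).
- Target range: 1/10,000 to 1/1000 (Sample Size).
- Calculated size 3000; planned size 10,000 (Sample Size).
- Class limits: rare from 0.01% (included) to 0.1%; very rare below 0.01% (Primary Outcome Measure).

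**Step 1. Reproduce the stated figure.** The rule gives n = 3/p.
- p = 1/1000: 3/0.001 = 3000. The exact form, ln(0.05)/ln(1 − p), gives 2995 after rounding up. The article's figure reproduces.
- p = 1/10,000: 3/0.0001 = 30,000 (exact 29,956). The article's figure does not reproduce; it is ten times too small for this end.

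**Step 2. What each size delivers.** The exact one-sided 95% upper bound with zero events is 1 − 0.05^(1/n). The chance of at least one case is 1 − (1 − p)^n.

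| n | 3/n | Exact bound, zero events | Chance at 1/1000 | Chance at 3/10,000 | Chance at 1/10,000 |
|---|---|---|---|---|---|
| 3000 | 0.1% | 0.0998% | 95.0% | 59.3% | 25.9% |
| 10,000 | 0.03% | 0.02995% | over 99.99% | 95.0% | 63.2% |
| 30,000 | 0.01% | 0.00999% | over 99.99% | 99.99% | 95.0% |

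So 3000 reaches 1/1000 and 10,000 reaches 3/10,000. Only about 30,000 would reach the lower end of the stated range. With a two-sided 95% interval the zero-event bound at 10,000 is slightly higher, 1 − 0.025^(1/10,000) = 0.0369%.

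**Step 3. Set this against the frequency classes at n = 10,000.**
- Zero events: the upper bound is 0.03%, which lies inside the rare class.
- One event: the point estimate is 1/10,000 = 0.01%, which the article counts as rare. The exact two-sided 95% interval is 0.00025% to 0.056%.
- More events move both the estimate and the upper bound up.

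No observed ADR can have a point estimate below 0.01%, and no result has an upper bound below 0.01%. The very rare class cannot be established with 95% confidence at this size.

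**The case against.** The strongest reply is that the operative size is 10,000, not 3000. On this view 3000 is correct arithmetic for one edge of the class and is superseded in the next sentence. The article prints the rule, so any reader can work out 3/10,000, and nowhere does it claim that 10,000 reaches 1/10,000. All of that stands: the planned size is not miscalculated, and it is ample for ADRs at 1/1000. It does not rescue the sentence that ties 3000 to the whole range, and the article never gives the limit that applies to 10,000.

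A second reply is that 3000 may come from the two guidance documents that the article cites. They are not available here, so this cannot be checked. The article nevertheless presents 3000 as the output of the rule it quotes, and on that basis it fails at the lower end.

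Four stronger readings are tempting, but the article does not support them.
- **Unseen ADRs will be labelled very rare.** No section says that an ADR that never occurred will be classified. The five classes are a standard scheme, and Table 2 most naturally describes ADRs that were observed.
- **Single-case ADRs will be falsely reassuring.** One event in 10,000 would be labelled rare, and its interval extends only downward, into the rarer class. The label is the more cautious of the two.
- **The liver and kidney outcomes rest on an inadequate 3000.** The liver section says "We will observe liver function in at least 3000 patients before and after medication" and the renal section sets the same minimum. These are floors, and neither section claims a detection limit.
- **Confidence intervals are missing.** A condensed article may leave interval reporting to the full protocol or analysis plan, so their absence here is not a fault.

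**Conclusion.** The sample-size statement is wrong as written. By the article's own rule, 3000 holds at 1/1000 and is short by a factor of ten at 1/10,000. The planned 10,000 is short by a factor of three at that end. What goes uncovered at the planned size is the band from 0.01% to 0.03%, the lower part of the rare class, together with everything below it.

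This is an error in the stated reach of the study, not in its size. Enrolment, data collection and the class given to any observed ADR do not change.

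The figures assume independent patients, complete ascertainment of each ADR and 10,000 evaluable patients. The Results section reports limited eligibility and missed follow-ups, so the evaluable number may be lower, and the bound 3/n then rises above 0.03%.

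**What to change.** Keep the sample size and rewrite the sample-size paragraph to state that:
- 3000 cases correspond to an ADR rate of 1/1000;
- the planned 10,000 correspond to 3/10,000, with a 63% chance of at least one case at 1/10,000.

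At reporting, recompute 3/n with the number of patients actually evaluable. Add one sentence to the primary outcome section: an ADR that was not observed is bounded at 3/n and is not to be reported as very rare.

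This needs no further patients and no new data. The cost is rewording and a stated detection limit that looks less favourable than the present text suggests. Covering the full rare range with 95% probability would instead take about 30,000 patients, three times the planned number, and the point does not require that.

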### Monitoring Time and Follow-Up

Patients are monitored throughout the medication period in the hospital. The treatment duration of PDL for URTI ranges from 3 to 14 days. This study will include a follow-up period of 7 days after the completion of observation treatment [26], aiming to assess the drug’s long-term efficacy and observe any delayed ADRs. The follow-up will be conducted either through face-to-face meetings or via telephone communication. We will use systematic methods and reminders to schedule appointments with patients.

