### Quality Control of ADRs

Each monitoring subcenter will formulate the first-level, quality-control rules and quality-control list according to the content of the monitoring program. The information system of each monitoring unit will be reviewed to ensure that the clinical study data are authentic and traceable. The implementation of the study will adhere to the research protocol and standard operating procedures in order to ensure the authenticity and reliability of the research data. The data collected are presented in Table 1.

**Table 1 table1:** Basic information form for administering Pudilan Xiaoyan oral liquid^a^.

Basic information	Before taking the medicine	After taking the medicine		
		7 days	14 days	21 days
Age	✓			
Sex	✓			
Smoking history	✓			
Occupation	✓			
Expense category^b^	✓			
Pathways to admission	✓			
Drinking alcohol	✓			
Western medicine diagnosis	✓			
Traditional Chinese medicine diagnosis	✓			
Past medical history	✓			
Personal history of allergies	✓			
Allergic manifestation	✓			
Previous other adverse drug reactions or events	✓			
Main drug combination: Western medicine, antibiotics, antipyretic analgesia, proprietary Chinese medicine, or other drugs		✓	✓	✓
Blood routine before and after treatment, white blood cell count, granulocyte, routine urine examination, liver function, renal function, ECG^c^ (test sheet within 30 days before treatment), C-reaction protein, influenza virus detection, pathogen detection, and other tests	✓	✓	✓	✓
Adverse reaction occurrence (yes or no)		✓	✓	✓

^a^Patients are visited and examined before and after taking the medication.

^b^Expense category refers to the classification of expenses, such as out-of-pocket (self-funded) costs, expenses covered by medical insurance, and other payment types. It helps in understanding how different types of expenses are categorized based on their funding source or payment method.

^c^ECG: electrocardiogram.

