##### Change in Renal Function

We will observation renal function in at least 3000 patients before and after medication. The renal function indexes will include creatinine and blood urea nitrogen. To observe whether the above renal function indexes appear abnormal after medication, the diagnostic criteria for acute kidney injury will be defined based on the Kidney Disease: Improving Global Outcomes serum creatinine criteria [32] (at least 50% increase in creatinine within 7 days or a 26.5 μmol/L increase within 48 h).

The time frame for all four result items is 7 days (Table 2).

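### Telephone follow-up conflicts with the blood tests in Table 1, so laboratory-only injury appearing after treatment could be missed in patients who still count in the ADR denominator

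*Protocol article*

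**What the plan says.** **Follow-up.** Under *Monitoring Time and Follow-Up*, the protocol article states: "Patients are monitored throughout the medication period in the hospital". It adds: "The treatment duration of PDL for URTI ranges from 3 to 14 days". It then says: "This study will include a follow-up period of 7 days after the completion of observation treatment". One stated purpose is to "observe any delayed ADRs". On how contact is made: "The follow-up will be conducted either through face-to-face meetings or via telephone communication". No rule says which patients receive which mode.

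**Table 1** (under *Quality Control of ADRs*). The row that begins "Blood routine before and after treatment, white blood cell count, granulocyte, routine urine examination, liver function, renal function" is ticked before medication and at 7, 14 and 21 days. The yes/no item for an adverse reaction is ticked in the same three post-dose columns. Footnote a reads: "Patients are visited and examined before and after taking the medication".

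**Outcomes.** The primary outcome is the incidence of ADRs, with 10,000 patients planned. *Change in Liver Function* defines drug-induced liver injury by biochemical thresholds. *Change in Renal Function* states that "the diagnostic criteria for acute kidney injury will be defined based on the Kidney Disease: Improving Global Outcomes serum creatinine criteria". Each section sets a floor of 3000 patients whose function is observed both before and after medication. The renal section ends by giving a 7-day time frame for all outcomes.

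**The concern.** A telephone call can record symptoms, but it cannot supply creatinine, ALT, alkaline phosphatase or bilirubin. If a call may take the place of a contact at which Table 1 expects blood tests, then an injury without symptoms that appears after treatment has no route to detection in that patient. It never reaches causality assessment and so cannot enter the ADR numerator, while the patient still counts among those monitored. Liver and kidney toxicity are the two organ risks that the Introduction and Discussion single out, and delayed reactions are a stated reason for the follow-up. A low reported rate could therefore partly reflect tests that were not done.

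**Working it through.** **1. The plan's own figure.** *Sample Size* uses the rule of three: 3 / 0.001 = 3000. The exact value is ln(0.05) / ln(1 − 0.001), which rounds up to 2995. The figure is reproduced and is not in dispute. The point is about the schedule and about who is tested.

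**2. Schedule against course length.** Inputs are courses of D = 3 to 14 days, follow-up from day D+1 to day D+7, and Table 1 columns at days 7, 14 and 21. The article does not say from when the columns count. I count from first dose, because the longest course plus follow-up is 14 + 7 = 21, which matches the last column.

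| Course length D | Follow-up window | Day 7 | Day 14 | Day 21 |
|---|---|---|---|---|
| 3–6 days | starts day 4–7, ends day 10–13 | follow-up | after follow-up ends | after follow-up ends |
| 7–13 days | starts day 8–14, ends day 14–20 | on treatment | follow-up | after follow-up ends |
| 14 days | day 15–21 | on treatment | on treatment | follow-up |

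Every course length has exactly one scheduled test in the period where a call is allowed. For courses of 3–6 days it is also the only scheduled post-dose test within observation.

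**3. The other way of counting.** If the columns ran from the end of treatment, day 7 would be the last day of follow-up for every course, and days 14 and 21 would lie outside it. No post-dose column would then fall on treatment. That reading widens the conflict.

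**4. The 7-day time frame.** Counting from first dose, day 7 falls on treatment for courses of 7–14 days (8 of the 12 course lengths) and in follow-up for courses of 3–6 days (4 of 12). These are counts of course lengths; the distribution of patients over them is not given.

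**5. Possible dilution.** Let q be the share of patients followed by telephone only, and s the share of laboratory-only injuries visible only after treatment. Neither is given. Assume that untested patients count as event-free, that all other injuries are found, and that contact mode is unrelated to injury. Then

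observed / true = 1 − q × s

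- q = 10%, s = 10%: 1 − 0.01 = 0.99
- q = 50%, s = 25%: 1 − 0.125 = 0.875
- q = 50%, s = 50%: 1 − 0.25 = 0.75
- q = 75%, s = 100%: 1 − 0.75 = 0.25

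The factor applies to laboratory-only injuries. Its effect on the overall ADR incidence is smaller and depends on how many ADRs are of this kind, which is also not given.

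**The case against.** The strongest defence has four parts.

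- **In-hospital monitoring.** Patients are monitored in hospital during medication, so injury arising then can be found. This stands. A reader might infer that laboratory-defined injury is undetectable in telephone patients, or that the liver and renal outcomes go unmeasured. The article does not support that: for courses of 7 days or more, day 7 falls on treatment.
- **The 3000-patient sets.** A patient without a post-medication sample has not been observed before and after, so the plain reading excludes unsampled patients, and all 3000 could be patients seen in person. This stands too. A reader might reduce the 3000 by an assumed telephone share of 25% to 75%, leaving 2250 to 750 tested and zero-event bounds of 0.13% to 0.40%. That needs unsampled patients inside the 3000, which the text does not say.
- **Coding.** A reader might infer that untested patients are entered as having no reaction. The article does not state how a missing test is coded, and a condensed article may leave that to the case report form.
- **Nature of Table 1.** The study is noninterventional, and the ticks may be fields for available results. *Instructions for Taking Medicine* also has patients checked before and after the medicine, which would allow an end-of-treatment sample even for short courses.

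The last part does not close the gap. No time is given for that later check, and an end-of-treatment sample would not show an injury appearing during the following 7 days. If the ticks are only fields for available results, a telephone patient still has blank laboratory fields beside a yes/no reaction item. The 3000-patient restriction protects the two secondary outcomes, but it does not reach the primary ADR incidence, for which the article states no such restriction.

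**Conclusion.** The concern holds in a limited form. The telephone option conflicts with the laboratory columns and the footnote of Table 1. As written, a liver or kidney injury that shows only in blood tests after treatment could be missed in a telephone-only patient who remains in the primary denominator. For courses of 3–6 days this reaches inside the 7-day time frame. For longer courses it affects only the test after treatment.

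The schedule result rests on counting days from first dose. The size of any dilution cannot be computed: the values from 0.99 to 0.25 are scenarios in q and s, and they also assume that untested patients count as event-free. If such patients were instead left out, the dilution would go, but the sampled patients might be a selected group. That patients with complaints return more often is plausible but not documented.

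**What to change.** - Reconcile *Monitoring Time and Follow-Up*, Table 1 with its footnote, *Change in Liver Function* and *Change in Renal Function* on which contacts include a blood sample and from when the 7-, 14- and 21-day columns count.
- State that the liver and renal outcomes, and the floor of 3000, count only patients with a baseline and a post-dose sample.
- Record contact mode on the case report form, and code telephone-only contacts as 'laboratory outcome not assessed'.
- Report ADR incidence in two parts: symptomatic events over all patients, and laboratory-defined events over sampled patients only.

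The cost is one extra form field and a smaller denominator for laboratory-defined events. No tests beyond Table 1 are needed.
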